### Data management

The IMBI Heidelberg is responsible for data management comprising all tasks concerning acquisition, processing, and utilization of data with the aim of guaranteeing high quality of the data and providing a valid data basis for the statistical analysis. The system used for data management is validated.

#### Data collection and transmission

Questionnaire, test, and interview data as well as body and fitness parameters will be sent regularly to the IMBI Heidelberg for data entry.

The m-health sensor data will be sent via “FileZilla – The free FTP solution” from all clinical sites to the Karlsruhe Institute of Technology (KIT) and from the KIT to the IMBI Heidelberg by an AES-256 encryption. Therefore, all clinical sites will get their own protected and secure access to save and transfer data. Only the respective clinical site and the KIT will have the authority to enter this access. Afterwards, the data will be transferred to the IMBI Heidelberg in the same protected way. In this case, only the KIT and the IMBI Heidelberg will have the authority to enter this access. Data are stored with pseudonyms only to protect participants. The security of the service is constantly checked by a security scan. The servers are hosted in a secure, ISO 27001 certified environment (datadock Strasbourg).

The app data on the smartphone is also encrypted (256 Bit). If a device gets lost, remote reset is possible. All communication to the web console is highly encrypted with SSL. The data are decrypted as soon as it is in the secure web console. The security of the service is constantly checked by a security scan. The servers are hosted in a secure, ISO 27001 certified environment. Data are stored with pseudonyms only to protect participants. The app data will be transferred from KIT to Heidelberg (IMBI) via “FileZilla” by an AES-256 encryption as well.

Participants are asked to place saliva samples in the freezer or deep-freezer compartment of their fridge and to bring them to the clinic at T2. Saliva samples will be centrifuged, frozen at − 20 °C, stored at the Department of Psychiatry, Psychosomatic Medicine and Psychotherapy, Goethe University, and sent for further analyses and storage to the Department of Psychiatry at University of Rostock. Saliva samples are transferred and stored with pseudonyms only to protect participants.

All findings including clinical data will be documented in the participant’s medical record and in the CRF. The investigator is responsible for ensuring that all sections of the CRF are completed correctly and that entries can be verified against source data (exception: questionnaire data are regarded as source data and part of the CRF at the same time). Any errors should have a single line drawn through them so that the original entry remains legible and the correct data should be entered at the side with the investigator’s signature, date, and reason for change. Self-explanatory corrections need not to be justified. The completed CRF must be reviewed and signed by the investigator named in the trial protocol or by a designated sub-investigator. The original CRF will be transferred to the data management of the IMBI within three weeks after each participant trial visit (T2–T5); one copy will remain with the investigator at the respective clinical sites.

#### Data handling

In order to ensure that the database reproduces the CRFs correctly, the IMBI accomplishes a double entry of data (with the exception of free text) performed by two different persons. The completeness, validity, and plausibility of data are examined by validation programs, which thereby generate queries. The checks to be programmed will be specified beforehand in a data validation plan. The investigator or the designated representatives are obliged to clarify or explain the queries. Any entry and correction in the study database will be reported automatically in an audit file. If no further corrections are to be made in the database, it will be closed (removal of write access) and used for statistical analysis. All data management activities will be done according to the current SOPs of the IMBI.

#### Storage and archiving of data

The database server of the IMBI Heidelberg with the stored data is located in a secure environment and protected by a firewall. During the trial, the data access is restricted to data entry staff and the data manager responsible for the trial. After database closure, the biometrician responsible for the trial gets access to the data for analysis. Backups are performed regularly.

The local investigators will archive all trial data (participant identification code list, source data, and investigator’s file) and relevant correspondence in the ISF. The ISF is kept at each study site. Separate ISFs will be provided for different adolescent and adult departments at the Goethe University, Frankfurt. At all other clinical sites, trial data for adolescents and young adults will be archived in one ISF. The ISF, all source data, and all documents indicated in section 8 of the ICH Consolidated Guideline on good clinical practice (GCP) (as applicable for the present study) will be archived after finalization of the trial according to the local legal regulations, at least for ten years. At the end of the trial, the PI will retain the originals of all CRFs. Trial-related documents will be archived locally. The trial master file will be archived at the Department of Child and Adolescent Psychiatry, Psychosomatics and Psychotherapy, Goethe University Hospital.

### Statistical methods

#### Primary outcome

Statistical methods are used to assess the quality of data, the homogeneity of the treatment groups, the efficacy endpoints, and the safety of the three treatment groups. The confirmatory analysis of the primary endpoint will be conducted on the basis of the ITT population. An additional analysis will be conducted for the per-protocol (PP) population that includes all participants without major protocol violations.

A closed testing procedure will be applied controlling the overall type I error rate at 0.05 (two-sided). A mixed model for repeated measures (MMRM) approach investigating the treatment effect with respect to all three intervention groups will be used. Two-group comparisons I-1 vs TAU, I-2 vs TAU, and I-1 vs I-2 based on contrasts will follow. Baseline IDS-C_30_, age, IQ, sex, treatment, and center will be included as covariates. The MMRM approach models jointly all actual observations without imputing missing data but using the within-participant correlation structure to provide information about unobserved post-baseline primary endpoints. Gender effects are of particular interest. If there are not enough events per category for the different covariates, gender effects will be excluded from the MMRM analysis and investigated in a secondary analysis. The MMRM approach, by which the missing values with respect to post-baseline primary outcomes are dealt with, demonstrates favorable characteristics in terms of type I error rate, power, and bias of estimates compared to alternative methods dealing with missing values, such as last-observation-carried-forward (LOCF) [98–100].

The first (global) hypothesis to be tested states that the change in the IDS-C_30_ total score is equal in all three treatment groups: H0: μI1 = μI2 = μTAU. This hypothesis will be tested at a two-sided level of significance of 5% against the alternative, H1: μI1 ≠ μTAU or μI2 ≠ μTAU or μI1 ≠ μI2. If the first null hypothesis can be rejected, the following three hypotheses for the two group comparisons will be tested simultaneously. One hypothesis to be tested states that the change in IDS-C_30_ total score between baseline (T2) and end of intervention (T4) is equal for I-1 and TAU: H0I1: μI1 = μTAU. This hypothesis will also be tested at a two-sided level of significance of 5% against the alternative hypothesis, H1I1: μI1 ≠ μTAU. A further hypothesis to be tested states that the change in IDS-C_30_ total score between baseline (T2) and end of intervention (T4) is equal for I-2 and TAU: H0I2: μI2 = μTAU. This hypothesis will again be tested at a two-sided level of significance of 5% against the alternative hypothesis, H1I2: μI2 ≠ μTAU. Another hypothesis to be tested states that the change in IDS-C_30_ total score between baseline (T2) and end of intervention (T4) is equal for I-1 and I-2: H0I3: μI1 = μI2. This hypothesis will also be tested at a two-sided level of significance of 5% against the alternative hypothesis, H1I3: μI1 ≠ μI2. The treatment comparisons for these three null hypotheses will be based on the contrasts between I-1 and TAU resp. I-2 and TAU resp. I-1 and I-2 at the end of the intervention (T4).

The above-described confirmatory approach controlling the type I error rate at 0.05 is pursued to enable a proof of efficacy already in this pilot study (for example, if the effect size is higher than anticipated). If the effect size is d = 0.5 as assumed for sample size calculation, the power to reject the null hypothesis of no difference in the primary endpoint comparing one novel intervention to TAU is only 70% (instead of 80%) as planning was performed at the more liberal level of 0.10.

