**Methods:**

This trial is a prospective, pilot phase-IIa, parallel-group RCT with three arms (two add-on treatment groups [BLT, EI] and one treatment as usual [TAU] control group). The primary outcome variable is change in the Inventory of Depressive Symptomatology total score (observer-blinded assessment) between baseline and ten weeks of intervention. This variable is analyzed with a mixed model for repeated measures approach investigating the treatment effect with respect to all three groups. A total of 330 participants with ADHD, aged 14 – < 30 years, will be screened at the four study centers. To establish effect sizes, the sample size was planned at the liberal significance level of α = 0.10 (two-sided) and the power of 1-β = 80% in order to find medium effects. Secondary outcomes measures including change in obesity, ADHD symptoms, general psychopathology, health-related quality of life, neurocognitive function, chronotype, and physical fitness are explored after the end of the intervention and at the 12-week follow-up.

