### Sample size calculation

The sample size calculation refers to the primary endpoint, more precisely, the expected change in the clinician-rated observer-blinded IDS-C_30_ total score between T2 and T4 in the intention-to-treat (ITT) population. The sample size calculation is based on the expectation to find a clinically relevant medium effect size (d = 0.5) with a two-sample t-test of at least one of the two interventions compared to TAU on the primary endpoint. As this is a pilot study to establish effect sizes, the sample size is planned at the liberal significance level of α = 0.10 (two-sided) and the power of 1-β = 80%. Taking into consideration the three-group design and an expected drop-out rate of about 30%, n = 219 participants will be allocated and analyzed. Based on the information received from the clinical study centers, it is expected that about 25–35% of the screened participants cannot be included in the study due to violation of inclusion/exclusion criteria. Hence, n = 330 participants will be assessed for eligibility. It can be expected that application of an analysis of covariance in the evaluation will reduce the standard deviation thus increasing the actual power of the study. Sample size calculation was done using ADDPLAN v6.1 [96].

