### Assignment of interventions

After written informed consent, participants are successively randomized to one of the three groups (BLT, EI, TAU). At each center, the trial coordinator generates the randomization code using a centralized web-based tool [97] which will be done at T2 after all baseline measurements have been completed in order to ensure allocation concealment. Randomization is a block randomization per center and is done in an allocation ratio of 1:1:1 with fixed block length and stratified for each participating center. The randomization list will be kept in safe and confidential custody at the Institute of Medical Biometry and Informatics (IMBI). Participants withdrawn from the trial will retain their identification codes (e.g. screening number, if already given). New participants must always be allocated a new identification code. As the proposed study is a non-pharmacological therapy intervention study, blinding of participants as well as therapists is not possible. However, the design is observer-blinded. Clinicians, who assess the primary outcome measure, the IDS-C30 total score, and the ADHD Rating Scale total score, are blind to treatment allocation. Therefore, at each site, randomization will be done only by the trial coordinator who is also the only person who will manage the investigator site file (ISF). Clinicians are not involved in the randomization procedure and are not allowed to receive information about group assignment. Clinicians will be provided with data recording sheets and data will be entered into the CRF by the trial coordinator. In addition, participants are instructed not to talk about their intervention at each visit. Adherence to randomization is monitored by an independent clinical on-site monitor, the Coordination Centre for Clinical Trials (KKS), University Hospital Heidelberg.

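### The stated 70% power for one intervention against TAU is the figure for a stand-alone t-test and leaves out the global test that must be rejected first

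*Protocol article*

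**What the plan says.** The Sample size calculation section of the protocol article plans for a medium effect, d = 0.5, tested "with a two-sample t-test of at least one of the two interventions compared to TAU on the primary endpoint". It adds that "the sample size is planned at the liberal significance level of α = 0.10 (two-sided) and the power of 1-β = 80" per cent. The total follows: "Taking into consideration the three-group design and an expected drop-out rate of about 30%, n = 219 participants will be allocated and analyzed". Under Assignment of interventions, randomization "is done in an allocation ratio of 1:1:1 with fixed block length".

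The confirmatory analysis in the Primary outcome section is stricter. The overall type I error rate is held at 5% two-sided by a closed procedure. The global null of equal change in all three groups is tested first at 5%. After that: "If the first null hypothesis can be rejected, the following three hypotheses for the two group comparisons will be tested simultaneously". Each pairwise test is also at 5%.

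The next paragraph refers back to this confirmatory approach and says that, at the planned d = 0.5, "the power to reject the null hypothesis of no difference in the primary endpoint comparing one novel intervention to TAU is only 70" per cent. The only reason given for the fall from 80% is that planning used alpha = 0.10.

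**The concern.** Under the stated procedure an intervention can be declared different from TAU only if two events occur together: the global test is significant and the pairwise contrast is significant. The power of that claim is the joint probability. It can never exceed the power of the pairwise test alone, and it is usually smaller. The change of alpha from 0.10 to 0.05 therefore explains only part of the loss. The gate takes a further share, and no power figure in the document includes it.

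What is at stake is how the confirmatory part of this pilot is read. Anyone weighing a non-significant result will take the miss rate at d = 0.5 to be 30%. For the procedure as written, and on the same basis as the protocol's own figure, it is higher by an amount that depends on how the other intervention performs.

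**Working it through.** **Inputs.** From Sample size calculation: d = 0.5; planning alpha 0.10 two-sided; power 80%; dropout about 30%; N = 219. From Assignment of interventions: 1:1:1, so 219/3 = 73 per arm. From Primary outcome: global test at 5%, pairwise tests at 5%, pairwise tests only after global rejection.

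**Step 1: reproduce the plan's figures.** For a two-sample t-test with n per arm, the noncentrality is d × √(n/2) on 2n − 2 degrees of freedom.

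- At alpha 0.10 and 80% power, d = 0.5 needs n = 50.1, so 51 per arm (actual power 80.6%).
- Dropout: 51/(1 − 0.30) = 72.9, so 73 per arm; 3 × 73 = 219. This matches the stated total exactly.
- At alpha 0.05 with n = 51: noncentrality 0.5 × √25.5 = 2.52 on 100 degrees of freedom, power 70.6%. With n = 50 it is 69.7%.

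The stated 70% is therefore the stand-alone t-test with about 51 evaluable per arm.

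**Step 2: power of the global test.** With 51 per arm, SD 1 and group means (0.5, m, 0), where m is the other intervention's true effect against TAU, the noncentrality is λ = 51 × Σ(mean − grand mean)². The test is F on 2 and 150 degrees of freedom at 5%.

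- m = 0 or 0.5: Σ = 0.1667, λ = 8.5, power 73.6%.
- m = 0.1 or 0.4: Σ = 0.14, λ = 7.14, power 65.5%.
- m = 0.25: Σ = 0.125, λ = 6.375, power 60.3%.

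For m between about 0.1 and 0.4 the global test alone falls short of 70%, so no claim that must pass through it can reach 70%.

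**Step 3: joint power.** I simulated 400,000 trials per scenario with 51 per arm and pooled variance, counting a success when the global F and the intervention-TAU contrast were both significant at 5%. The Monte Carlo standard error is about 0.1 point.

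| Other arm's true d | Global test alone | Closed test, one intervention vs TAU |
|---|---|---|
| −0.25 | 93.8% | 70.2% |
| 0 | 73.7% | 64.9% |
| 0.1 | 65.4% | 61.3% |
| 0.2 | 60.9% | 59.0% |
| 0.25 | 60.2% | 58.6% |
| 0.3 | 60.8% | 58.9% |
| 0.4 | 65.5% | 61.3% |
| 0.5 | 73.6% | 64.8% |
| 0.6 | 82.7% | 67.6% |
| 0.75 | 93.7% | 70.3% |

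The ungated contrast in the same simulations has about 71% power throughout.

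**Step 4: sensitivity to evaluable n.** Over other-arm effects from 0 to 0.5, the closed-test range is 57.6–63.8% with 50 per arm, 58.6–64.9% with 51, and 59.7–65.8% with 52.

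**The case against.** **The planned analysis is not an unadjusted completers' t-test.** It is an MMRM with baseline IDS-C30 and other covariates that also uses T3 data from dropouts, and the Sample size calculation section expects covariance adjustment to raise power. This stands against any attempt to read 35–41% (100 minus 59–65) as the trial's true chance of missing d = 0.5. The document gives no size for the gain, so the true power is unknown. As an illustration, with an assumed covariate-outcome correlation r, the effective d is 0.5/√(1 − r²). At r = 0.30 the ungated power is about 75% and the gated power about 63–69%. At r = 0.45 they are about 80% and 70–76%. The gain does not rescue the stated figure: the 70% contains none of it, and the gate still costs several points.

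**The other arm's effect is not fixed by the protocol.** This is correct. A reader might take 59–65% as an unconditional correction, but it holds only for an other-arm effect between 0 and 0.5.

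**The sample size section has a different target.** A reader might infer that the 80% there and in the abstract is wrong too. The documents do not support that. Both places present alpha = 0.10 as a planning level, and the sample size section names its test and its target: "with a two-sample t-test of at least one of the two interventions compared to TAU on the primary endpoint". For at least one success against TAU the gated power at 5% is 66.7% if the other arm equals TAU, 59.5% if it has d = 0.25, and 73.6% if both have d = 0.5. The figures in the table above belong to the sentence about one intervention only.

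**The 70% is offered as a caveat.** It might be read as the justification for seeking proof of efficacy in a pilot. It is not: the stated motive is that the effect could turn out larger than assumed, and the reader is warned that power at d = 0.5 falls short of 80%. Nor does the document say that a non-significant result would be taken as no effect.

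**All 219 are to be analysed.** With 73 fully informative participants per arm the gated power would be 76–82% and the ungated 85%. The stated 70% plainly assumes 51 per arm, so this does not explain it.

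**Conclusion.** The point holds in a limited form. The 70% is correct arithmetic for a test that the confirmatory plan does not run on its own, and it is presented as the power of the procedure that the plan does run. On the protocol's own unadjusted basis (51 evaluable per arm, d = 0.5 for the tested arm, equal variances), closed-test power is about 59–65% when the other intervention's true effect lies between 0 and 0.5. That is 5 to 11 points below the stated figure and beyond rounding. Outside that range of other-arm effects the gap narrows, and it closes at about −0.25 and 0.75.

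Severity is moderate. The closed procedure still controls type I error, and the phase-III decision is tied in the Abstract and Discussion to establishing at least medium effects, not to a power figure.

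**What to change.** Amend the one sentence in the Primary outcome section, in either of two ways:

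- Replace the 70% with the conditional closed-test figure. For example: with d = 0.5 and 51 evaluable participants per arm, the power of the closed test to declare one intervention different from TAU is about 65% if the other intervention's true effect is 0 or 0.5 and about 59% if it is 0.25, before any gain from covariates or the MMRM.
- Keep the 70%, label it as the power of a stand-alone two-sample t-test at 5%, and give the gated range of about 59–65% beside it with the same condition on the other arm.

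In both cases the explanation of the loss from 80% should name the global test as well as the change of alpha. The cost is wording and a less favourable number. No change is needed to the sample size, the tests, the abstract or the Sample size calculation section.

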#### Additional analyses

Descriptive methods will be used for the analysis of the secondary outcomes, including the calculation of appropriate summary measures of the empirical distribution (mean, standard deviation, median, minimum and maximum for continuous variables, and frequency in percentages for categorical variables) as well as calculation of descriptive two-sided *p* values. A special focus of the exploratory analysis will be with respect to the time course of the primary as well as the secondary endpoints. Additionally, sensitivity analyses will be conducted for different populations (PP population, appropriate subgroups) and applying different imputation techniques (such as LOCF) for missing values. Further exploratory analyses will be performed to identify intervention effects in subgroups and potential prognostic factors (including hormone levels) for an intervention effect. Furthermore, variables possibly mediating treatment effects such as reward processing, stress reactivity, and compliance with the interventions will be explored. Appropriate regression will be used following the four-step procedure by Baron and Kenny [101]. Graphical methods will be applied to visualize the findings of the study. The safety analysis will be based on the set of all randomized participants who were exposed to study intervention at least once and includes calculation and comparison of frequencies and rates of adverse and serious adverse events reported in the two intervention groups. All analyses will be done using SAS version 9.4 or higher. A statistical analysis plan will be written before the final analysis.

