It is hypothesized that the two manualized ten-week interventions will result in a smaller increase of depressive symptoms and obesity compared to a treatment as usual (TAU) control condition. In addition, pre-existing depressive symptoms and obesity are expected to decrease after ten weeks of either BLT or EI compared to TAU. TAU includes ten weeks of stable pharmacotherapy, group-based or individual CBT (not including elements of BLT or EI). To assess the stability of these secondary prevention effects, follow-up assessment will be done 12 weeks after the end of the intervention. Furthermore, immediate and long-term intervention effects on core ADHD symptoms, general psychopathological symptoms, health-related quality of life, neurocognitive function, chronotype, body-related measures such as blood pressure and heart rate, physical fitness, and hormone concentrations will be assessed. Variables possibly moderating treatment effect, including age, sex, medication, physical fitness and activity, daily light exposure, chronotype, and mood regulation will be explored as well as variables possibly mediating treatment effects, such as reward processing, stress reactivity, and compliance with the intervention.

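### Mediation is to be explored with the four-step procedure, which as commonly applied screens on a significant total effect and gives no estimate or interval for the indirect effect

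*Protocol article*

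**What the plan says.** The Background section lists, among the things to be explored, "variables possibly mediating treatment effects, such as reward processing, stress reactivity, and compliance with the intervention". The section Additional analyses repeats this ("variables possibly mediating treatment effects such as reward processing, stress reactivity, and compliance with the interventions will be explored") and names the method: "Appropriate regression will be used following the four-step procedure by Baron and Kenny". It gives no significance level for the steps and mentions no estimate, test or interval for the indirect effect.

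Two other sections bear on the first step. Sample size calculation plans for a "clinically relevant medium effect size (d = 0.5) with a two-sample t-test", at "the liberal significance level of α = 0.10 (two-sided) and the power of 1-β = 80"%. Primary outcome then tests at 0.05 two-sided and concedes that at d = 0.5 "the power to reject the null hypothesis of no difference in the primary endpoint comparing one novel intervention to TAU is only 70"%.

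**The concern.** Asking whether a variable mediates the treatment effect means asking whether the indirect effect is zero. The indirect effect is the treatment-to-mediator path (a) times the mediator-to-outcome path (b). The four steps test (1) the total effect, (2) path a, (3) path b given treatment, and (4) whether the direct effect (c') is no longer significant. None of them estimates a × b.

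Two things follow if the procedure is applied in its usual form:

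- Step 1 screens on a different null hypothesis. A finding of no mediation may then mean only that the total effect missed significance.
- Step 4 treats absence of evidence for a direct effect as evidence that there is none. A finding of complete mediation may then mean only that the direct-effect test lacked power.

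At stake is what the mechanism results can contribute to planning a phase-III trial. An indirect effect with an interval would be usable there; a chain of significance decisions is much less so.

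**Working it through.** **1. Reproduce the plan's own figures.** Inputs from Sample size calculation: d = 0.5, two-sample t-test, two-sided alpha 0.10, power 80%, drop-out about 30%, 219 participants. Allocation is 1:1:1 (Assignment of interventions).

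The noncentrality is d × √(n/2). With n = 51 per arm it is 0.5 × √25.5 = 2.52, on 100 degrees of freedom.

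- Alpha 0.10: power 80.6% (50 per arm gives 79.9%, so 51 is the minimum).
- Drop-out: 51 / 0.70 = 72.9, so 73 per arm, and 3 × 73 = 219. This matches the protocol.
- Alpha 0.05: power 70.6%. This matches the stated 70%.

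**2. What step 1 blocks at d = 0.5.** If step 1 must be significant, the whole procedure cannot succeed more often than step 1 does.

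| Setting for step 1 | Power | Blocked |
|---|---|---|
| alpha 0.05, 51 per arm, unadjusted | 70.6% | 29.4% |
| alpha 0.10, 51 per arm, unadjusted | 80.6% | 19.4% |
| alpha 0.05, 51 per arm, adjusted, assumed covariate-outcome correlation 0.5 | 82% | 18% |
| alpha 0.05, 73 per arm (no drop-out), unadjusted | 85.1% | 14.9% |

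For the adjusted row, the residual SD is √(1 − 0.5²) = 0.866, so the effective d is 0.5 / 0.866 = 0.577. Assumed correlations of 0.3 and 0.7 give power of 75% and 94%. None of these rows needs an assumption about the paths.

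**3. What dropping step 1 would gain.** This does need path sizes, and the article gives none, so they are assumed here. Simulated model: X = 0/1 with 51 per arm; M = aX + N(0,1); Y = c'X + bM + √(1 − b²) N(0,1). The within-arm SD of Y is 1 and c' = 0.5 − ab, so the total effect is always d = 0.5. All tests are at 0.05 without covariates.

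| a | b | c' | Detected without step 1 | Steps 1 to 3 all significant | Gain (points) |
|---|---|---|---|---|---|
| 0.39 | 0.39 | 0.35 | 51% | 41% | 10 |
| 0.5 | 0.3 | 0.35 | 61% | 47% | 14 |
| 0.5 | 0.5 | 0.25 | 70% | 56% | 14 |
| 0.8 | 0.4 | 0.18 | 97% | about 70% | about 27 |
| 1.0 | 0.5 | 0 | 99.9% | 71% | 29 |

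Rows 1, 2 and 4 use a 95% percentile bootstrap interval for a × b. Rows 3 and 5 use joint significance of a and b. Where both were run they agree closely: the joint test gives 49% against 40% in row 1 and 97% against 69% in row 4.

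With a large direct effect (a = 0.8, b = 0.4, c' = 0.5, so total 0.32 + 0.50 = 0.82) the comparison is 97% against 95%, and the gain is almost gone. When one path is zero, the joint test rejects in 4.7% to 5.4% of runs and the bootstrap interval in about 5%, so the gain is not bought with many false findings.

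**4. Step 4.** Take a = 0.5, b = 0.4 and a true direct effect of 0.30. The total is 0.20 + 0.30 = 0.50, so 60% of the effect is direct. Steps 1 to 3 pass in 53.2% of runs, and in 29.0% of runs they pass and the direct effect is also non-significant. So 29.0 / 53.2 = 55% of the passing runs would be called complete mediation although most of the effect is direct.

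**The case against.** The strongest reply has four parts.

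*The rules are partly read in.* The article says only that mediators will be explored by regression following the procedure. It does not say that the analysis stops after step 1, sets no alpha for the steps, and does not say it will declare complete mediation. This stands in part: the figures above apply to the procedure in its usual form, at an assumed alpha. But a named procedure carries its usual rules unless they are changed, so this is a stated choice and not merely a detail left open.

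*The 70% is not a fixed ceiling.* A reader might infer that the mediation analysis can never exceed 70%. The documents do not support that. The 70% refers to an unadjusted t-test at 0.05, whereas Sample size calculation expects covariance analysis to raise power and Primary outcome adjusts for baseline IDS-C30, age, IQ, sex and center. If step 1 is adjusted in the same way, the block shrinks as shown in the working.

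*The contrast depends on the mediator.* A reader might also infer that real mediation at the planned d = 0.5 is missed about 30% of the time where a direct test would miss about 3%. That pair belongs to one assumed strong mediator (a = 0.8, b = 0.4). With a = 0.5 and b = 0.3 the joint test misses 39% and the four-step rule 54%; with a = 0.5 and b = 0.2 the figures are 64% and 73%. Nothing in the documents favours the strong case.

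*It is exploratory, and an analysis plan is to follow.* This stands and limits the weight of the point. The primary test, the sample size and the safety analysis are untouched. So is the condition for a phase-III trial, which concerns effects on depressive symptoms and obesity. Someone who reports all the regressions also has both coefficients of the product already. It does not rescue the choice of method: in exploratory work an estimate with an interval is more useful than a significance screen, and an analysis plan that follows the protocol would inherit the screen.

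**Conclusion.** The point holds in a limited form. The named procedure suits the stated question poorly: as commonly applied it requires a significant total effect, yields no estimate or interval for the indirect effect, and reads a non-significant direct effect as complete mediation.

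The part that rests on the protocol's own numbers is the step-1 block: about 29% at d = 0.5, assuming an unadjusted test, alpha 0.05 and 51 evaluable per arm, and less under the other settings examined. The size of the gain from dropping step 1 rests on assumed paths. It is about 10 to 30 points with total d = 0.5 and no adjustment, and close to nothing when the direct effect is large. What is affected is the interpretation of the exploratory mediation results only.

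**What to change.** In Additional analyses, replace the reference to the four-step procedure with wording such as:

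*For each intervention versus TAU, the indirect effect (the product of the treatment-to-mediator and mediator-to-outcome coefficients, adjusted for baseline IDS-C30, the baseline value of the mediator where one exists, and the model covariates) will be estimated with a 95% percentile bootstrap confidence interval. A significant total effect is not required. The direct effect will be reported with its confidence interval, and complete mediation will not be concluded from its non-significance. These analyses are exploratory.*

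The condition on the baseline value is there because compliance with an intervention has none. How compliance is to be contrasted with TAU at all is a separate question that this wording does not settle.

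The cost is this short text in the protocol or analysis plan and a short bootstrap program on the same regressions. No further data or participants are needed. The small downside is that more mediators may be flagged when the total effect is not significant, which is why the exploratory label should stay attached to the results.
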